### Serious adverse events (SAEs)/reactions

SAEs or reactions are defined as any untoward medical occurrence or effect that at any dose results in death, is life threatening, requires hospitalization or prolongation of existing inpatient hospitalization, results in persistent or significant disability or incapacity, or is a congenital anomaly or birth defect.

Should a study participant become pregnant while undertaking the trial, or aid in the conception of a child while they are participating in the trial, the pregnancy and resulting child should be followed up for a period of no less than 18 months. In this trial should a child be followed up and diagnosed with MFS, this would not be considered unexpected due to the nature of the syndrome.

### Expected SAEs (as a result of the underlying disease)

Expected SAEs as a result of the underlying disease include: admission or procedure for MFS including treatment for cardiovascular, musculoskeletal, ocular, and thoracic complications; aortic dissection; aortic regurgitation requiring surgery; emergency or elective aortic root and/or valve replacement surgery; cerebrovascular accident; and cardiovascular death, sudden death, or death during surgery.

Expected SAEs will be reported as per the usual data capture requirements for the study and are not subject to expedited reporting.

Other SAEs which are not expected irrespective of causality will be subject to SAE reporting requirements. In the event of an SAE, investigators will report details on the SAE form on the eCRF including date of event, admissions, diagnosis details, date of discharge, or death. SAE reports must be completed within 24 hours of the investigator’s knowledge of the SAE. Investigators will be able to submit follow-up SAE reports should further information become available. Investigators will be expected to assess and assign causality and expectedness of each event on the form using the definitions described below. The CTEU will review all SAE reports. The Chief Investigator/deputy will review the SAE reports and inform the CTEU of the assessment.

### Definitions for assessment of causality

The definitions for assessment of causality include:

1. Unrelated: there is no evidence of any causal relationship

2. Unlikely: there is little evidence to suggest there is a causal relationship (for example the event did not occur within a reasonable time after administration of the trial medication). There is another reasonable explanation for the event (for example the patient’s clinical condition, other concomitant treatment)

3. Possible: there is some evidence to suggest a causal relationship (for example because the event occurs within a reasonable time after administration of the trial medication). However, the influence of other factors may have contributed to the event (for example the patient’s clinical condition, other concomitant treatments)

4. Probable: there is evidence to suggest a causal relationship and the influence of other factors is unlikely

5. Definitely: there is clear evidence to suggest a causal relationship and other possible contributing factors can be ruled out

6. Not assessable: there is insufficient or incomplete evidence to make a clinical judgement of the causal relationship.

### Suspected unexpected serious adverse reactions (SUSARs)

A serious adverse reaction (SAR) can be considered unexpected when the AR is not consistent with the applicable product information or expected SAEs listed above. All SUSARs related to an IMP, which occur during the trial, are subject to expedited reporting. Where applicable, if an event is considered a SUSAR, the patient should be unblinded from the study allocation.

### Reporting of SUSARs

A full and detailed account of the SAE must be recorded on the SAE report. The SAE report must be completed within 24 hours. A medical summary should also be faxed to the CTEU within 24 hours. The Chief Investigator/deputy will review the report and summary and inform the CTEU of the assessment.

### Expedited reporting of SUSARs

All SUSARs will be reported to the Medicines and Healthcare Products Regulatory Agency (MHRA) and NHS Research Ethics Committee (REC) by the CTEU. All SUSAR reports will be unblinded prior to submission. A SUSAR which is fatal or life threatening will be reported to the MHRA and the main REC by the CTEU as soon as possible and within 7 days of knowledge of the event. A SUSAR which is not fatal or life threatening must be reported to the MHRA and the main REC as soon as possible and within 15 days of knowledge of the event. The CTEU will inform all relevant parties of any reported SUSARs within 15 working days.

### Annual reporting

The CTEU will submit annual safety reports of all suspected SARs in accordance with regulatory requirements to the MHRA and the main REC. Annual safety reports will be submitted to the MHRA on the date of the original clinical trials authorization. Annual progress reports will also be submitted to the main REC. There is no requirement for local trial sites to submit progress reports to local RECs.

By inspection of this table, to detect a 0.5 mm change in dilatation rate would require 204 patients in each group. Allowing for a 20% drop-out (including missing data and non-compliance) we aim to recruit 245 patients in each group, making a total of 490 patients. Expansion rates according to treatment group would be regularly reviewed by the independent Data and Safety Monitoring Committee (DSMC) who would advise the Steering Committee if there was clear evidence of benefit before the scheduled end of the study, or alternatively may advise if there is no real possibility of finding a difference (performing a 'futility’ analysis) either because irbesartan does not have the expected effects, or if aortic expansion rates are slower than expected in the control group. We have selected a proportional reduction of 50% of dilatation rate per annum (0.5 mm) largely on pragmatic grounds. If irbesartan only offered a very modest reduction in rate we are much less certain that this could be translated into a clinical benefit. We are also measuring a surrogate outcome (aortic dilatation) but one which is closely related to adverse clinical events in this population.

### Statistical analysis

The primary analysis in this study is the comparison of the rate of annual aortic dilatation in those patients treated with irbesartan compared to placebo. The annual rate of dilatation will be calculated by estimates of mean values of the annual echocardiograms adjusting the time of follow-up to a 'common’ start point, that is, the baseline measurement. An independent samples *t*-test will be used to test for a difference in the rate between the irbesartan and placebo groups, assuming that the measurement of annual dilation follows a normal distribution. Analysis of covariance (ANCOVA) will be used if the analysis of the primary outcome is adjusted for any other variables. The primary analysis will be carried out according to the intention-to-treat principle in which all randomized patients will be included according to their initial randomized allocation irrespective of whether they continue to take the assigned treatment or not. Patients who are not followed up to the end of the study for whatever reason will have the last echo measurement included in the analysis. Patients will be followed from the time of randomization to the end of the study period. Thus individual patients will have a variable follow-up period. No formal method for imputing missing aortic diameter values is proposed as the comparison will be performed on the mean of group data. Secondary analyses include comparison of other measurements using appropriate comparative and descriptive statistics.

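### Comparing group means does not excuse missing echoes, and a t-test on rates cannot include every randomized patient; a mixed model on all echoes would serve better

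*Protocol article*

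**What the plan says.** All of the analysis wording is in the protocol article, *Statistical analysis*.

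- Test: an independent-samples t-test "will be used to test for a difference in the rate between the irbesartan and placebo groups".
- Rate: "The annual rate of dilatation will be calculated by estimates of mean values of the annual echocardiograms adjusting the time of follow-up". Time is counted from the baseline echo. No per-patient slope, weighting or model is stated.
- Population: intention to treat, meaning that "all randomized patients will be included according to their initial randomized allocation irrespective of whether they continue to take the assigned treatment or not".
- Early leavers: "Patients who are not followed up to the end of the study for whatever reason will have the last echo measurement included in the analysis".
- Unequal follow-up: "Thus individual patients will have a variable follow-up period".
- Missing values: "No formal method for imputing missing aortic diameter values is proposed as the comparison will be performed on the mean of group data".

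Elsewhere, *Sample size calculation* allows for a "20% drop-out (including missing data and non-compliance"). *Withdrawal from trial procedures and incomplete follow-up* expects that some outcome data will not be captured. Echoes are done at baseline and then yearly (*Primary outcome measure*, Table 1). Planned follow-up is 36 to 60 months (*Enrolment and participating centers*).

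**The concern.** Two statements in the primary analysis do not stand as written.

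First, the reason given for having no missing-data method is that means are compared. The mean of the observed patients estimates the mean of all patients only if those who are missing grow at the same rate as those who are seen. Taking an average does nothing to secure that.

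Second, the first post-baseline echo is at month 12. A patient lost before then has no rate. With no imputation, that patient cannot enter a t-test on rates, so the promise to include everyone cannot be kept. The result would be a complete-case comparison carrying an intention-to-treat label.

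A smaller matter follows from the last-echo rule. It keeps early leavers in, but with a rate based on one or two years. An ordinary t-test counts that rate the same as one based on three to five years, although it is noisier. What is at stake is how the confirmatory result is described, some exposure to dropout bias, and some precision that echoes already in the schedule could provide.

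**Working it through.** **The plan's own figure.** n per group = 2(1.96 + 0.84)² × 1.8² / 0.5² ≈ 203.4, so 204, as Table 2 states. After the plan's own 20% loss, 245 × 0.8 = 196 per group remain and power is 78.5%, so there is little precision to spare.

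**Patients with no rate.** Assumptions: the 20% loss is spread evenly over annual visits, and half of patients are due three and half four annual echoes. The share lost before the first follow-up echo is 0.5 × 20%/3 + 0.5 × 20%/4 = 3.33% + 2.50% = 5.83%. Of 490, that is 28.6 patients. The ceiling, if the whole allowance were lost before month 12, is 98 of 490.

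**Can missing rates bias a comparison of means?** Suppose a share m of a group has no rate and those patients grow g mm/yr faster than the rest. The observed mean is then too low by m × g. With no true effect, the observed difference between groups is (difference in m) × g.

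- 8% against 4% missing (about 6% on average), g = 1 to 3: 0.04 × g = 0.04 to 0.12 mm/yr.
- 20% against 10% missing, g = 1 to 3: 0.1 to 0.3 mm/yr, or 20 to 60% of the 0.5 mm target. This is extreme, because it needs one arm to lose the full 20% before any follow-up echo.
- Equal shares and equal g: zero.

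The shares and g are assumed. The point is that averaging does not make the bias zero; similarity of the missing patients would.

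**Loss through surgery, with the last-echo rule applied.** Simulation under assumed values: entry diameter uniform 34 to 45 mm, true slope SD 0.8 to 1.2, measurement SD 1 to 2 mm, leaving at a measured 50 mm, and rate = (last − baseline) / actual time. A true difference of 0.50 is seen as 0.50 to 0.53 mm/yr if the 50 mm echo is used, and 0.47 to 0.49 if it is not. Fewer than 0.4% of patients have no rate for this reason.

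**Precision.** For a baseline-to-last rate over T years, Var = s_b² + 2s_e²/T², where s_b is the SD of true slopes and s_e the measurement SD. The article gives neither, only a total SD of 1.8 from patients followed 0.9 to 5.1 years (quartiles 2.4, 3.4, 4.5).

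1. With T uniform within each quarter, the mean of 1/T² between a and b is 1/(ab). The average of 1/(0.9×2.4), 1/(2.4×3.4), 1/(3.4×4.5) and 1/(4.5×5.1) is (0.463 + 0.123 + 0.065 + 0.044)/4 = 0.174.
2. So s_b² = 3.24 − 2 × 0.174 × s_e². At s_e = 1.5 this is 2.46. The variance of a rate is then 2.46 + 4.5/1 = 6.96 at one year and 2.46 + 4.5/16 = 2.74 at four years.
3. With the follow-up mix above (5.83% stopping after each of none, one and two follow-up echoes; 42.5% ending at year 3, including late leavers; 40% at year 4), the cut in variance of the treatment contrast, against equal-weight last-minus-first rates, is:

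| s_e (mm) | cut in variance |
|---|---|
| 1.0 | about 2% |
| 1.5 | about 7% |
| 2.0 | about 15 to 17% |
| 2.7 | about 37 to 41% |

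The ranges reflect how the mixed model is approximated. Most of the gain comes from weighting by follow-up time.

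**The case against.** The best defence is the last-echo rule. A fast dilator who goes to surgery normally has at least one follow-up echo and so keeps a rate. Entry requires a diameter below 4.5 cm and the usual surgical threshold is 50 mm, so few would leave before month 12. A reader might infer that surgery seriously biases the comparison; the check above does not support that.

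A reader might also infer that the design sets one-year patients against five-year patients. It does not. Minimum planned follow-up is 36 months, and one-year rates arise only through early loss. For planned follow-up of three to five years alone, equal weighting keeps 92 to 99% efficiency when measurement error makes up 25 to 75% of the variance.

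The wording on how the rate is built is loose, so last-minus-first for complete patients is an inference. The standardized echo protocol and blinded core laboratory may also keep measurement error low. A mean of 1 with SD 1.8 would put 29% of rates below zero under normality, which hints at noise but does not prove it. All of this stands.

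Finally, model choice and sensitivity analyses are often left to a statistical analysis plan. That does not answer the main point: the article itself gives a reason and an inclusion rule, and neither works.

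**Conclusion.** The concern holds at moderate severity. Two things need no assumption: the rationale for ignoring missing echoes is wrong, and patients without a follow-up echo cannot be in the t-test. How many such patients there are (about 6%) depends on assumed dropout timing. Bias from surgery is likely to be a few hundredths of a mm/yr, provided the last echo is divided by actual elapsed time, which the text does not spell out. Bias from patients with no rate at all cannot be sized from the document and is zero if the arms lose similar patients in similar numbers.

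Equal weighting is a loss of precision and not a bias: about 2 to 7% of the contrast variance at a measurement SD of 1.0 to 1.5 mm. Larger losses need 2 mm or more, for which the document gives no evidence. It would be too much to say that the primary result is invalid.

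**What to change.** 1. Make the primary analysis a linear mixed model on all native-root echoes at actual scan dates, with random intercept and slope, a common baseline mean (the baseline echo precedes randomization), and treatment-by-time as the estimated difference in annual rate. It is valid under missing-at-random and weights patients by the information they carry.
2. Delete the rationale that rests on group means.
3. State plainly that patients with only a baseline echo enter the model but add little information on slope, so that the intention-to-treat claim is not oversold.
4. Add a delta-adjusted, missing-not-at-random sensitivity analysis.
5. Keep the t-test on per-patient rates as a supportive analysis.

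The cost is revised wording and slightly more analysis work. The model assumes linear growth, which the supportive analysis helps to check. No new data are needed.

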### Regulatory and ethical considerations

#### Regulatory framework and approval

This study is a randomized trial of an IMP (licensed product in new conditions of use; new dosing schemes/new target population), and as such will comply with the European Clinical Trials Directive and the Medicines for Human Use (Clinical Trials) Regulations 2004. A clinical trial authorisation (CTA) has been granted from the MHRA. The study is registered in the European Clinical Trials Database with a European Union Drug Regulating Authorities Clinical Trials (EudraCT) number.

#### Ethical approval

The trial will comply with the Declaration of Helsinki (http://www.wma.net/) on research involving human subjects. The study protocol, patient information sheet, and consent form have been approved by the NHS National Research Ethics Service (NRES) and subsequently the research and development departments of each participating center for site-specific approval. The AIMS trial is also approved on the National Institute for Health Research (NIHR) portfolio.

### Monitoring

#### Initiation visit

Before the study commences, each trial site will receive a training visit from the CTEU where required. The purpose of these visits will be to ensure that the local research team (local principal investigator, co-investigators, study coordinator, and pharmacists) fully understand the protocol, eCRF, and the practical procedures for the study.

### Interim monitoring visits

At regular intervals during the study, the CTEU will perform monitoring visits to each trial site. The purpose of these visits is to ensure compliance with the protocol and that ethical and regulatory requirements are met. Source data verification (SDV) and checking of essential documents will be performed. Monitors will also visit the pharmacy departments to review study procedures, storage, and accountability of the IMP.

Monitoring visits also provide an opportunity for further training if required (for example new staff). Central review of study data will also be performed throughout the study by the data management team at the CTEU.

#### Closeout visit

At the end of the study, each trial site will receive a closeout visit from the CTEU to resolve any outstanding edit queries or AEs and to verify the archiving procedures for study documentation.

### Trial Steering Committee (TSC)

The main role of the TSC is to monitor and supervise the progress of the trial. The composition of the TSC will comply with Medical Research Council (MRC) guidelines with an independent Chair and lay representation as well as the Chief Investigator and main co-investigators. The TSC will meet regularly throughout the study.

### Data Monitoring Committee (DMC)

All members of the DMC are independent of the trial. The DMC will meet prior to the start of the trial and then one and two thirds of the way through the trial, or as required thereafter. The DMC will be expected to develop, in agreement with the investigators, a charter outlining their responsibilities and operational details.

### Study coordination

The study will be coordinated and managed by the CTEU, a dedicated clinical trials department within the Royal Brompton Hospital. In addition to providing overall project coordination, the CTEU will assist in preparing the final protocol, the investigators’ manuals, design the eCRF, provide the randomization service and design, and instigate the data management system. The CTEU will ensure that the trial runs according to the pre-agreed timetable, recruitment targets are met, eCRFs are completed accurately, compliance with relevant ethical and regulatory standards, and that all aspects of the study are performed to the highest quality. The CTEU will also assist in the training of investigators and coordinators at the start-up of the study and for performing monitoring and pharmacovigilance procedures throughout.

### Investigators’ responsibilities

Investigators are required to ensure compliance to the protocol and all statutory regulations and guidelines, eCRFs, and manual of operations. Investigators are required to allow access to study documentation or source data on request for monitoring visits and audits performed by the CTEU, sponsor, or any regulatory authorities.

### End of trial

The end of trial will be declared when the last patient recruited completes the last follow-up visit, that is, echocardiogram at 36 months follow-up visit.

### Investigational medicinal products

#### Manufacture

The study drug (irbesartan and placebo) will be purchased from the commercial supplier, Sanofi-Aventis, Guildford, Surrey, UK, which holds the manufacturing license to produce the IMP.

Brecon Pharmaceuticals Ltd, Hay-on-Wye, UK, will undertake to prepare, pack, and label the IMPs and distribute as required throughout the trial. The IMP supply will be labeled in accordance with regulatory requirements and specifications and will be approved by the MHRA as part of the application for CTA.

### Storage and dispensing

The study drug patient kit for the 1-month run-in phase, baseline phase, and uptitration phase (month 1 to 3) will be stored in a secure area of the pharmacy, under the conditions described in the respective SmPC.

The IMP supply will be dispensed by the local pharmacy which will be responsible for maintaining a record of accountability.

Continuation packs of the study drug will be dispensed direct to patient homes on a 3-month supply basis by Brecon Pharmaceuticals Ltd. Drug accountability records will be supplied as required.

### Publication policy and dissemination of results

The results from the trial will be submitted for publication in a major journal irrespective of the outcome. The TSC will be responsible for approval of all manuscripts arising from the study prior to submission for publication. Sub-studies of center-specific data may only be carried out with the knowledge and approval of the TSC. Sub-study publications must not be published prior to the publication of the main study.

All publications and presentations will make appropriate acknowledgement of the contribution of the collaborative group. At the end of the study, patients will be able to request a copy of the results of the study from the investigator at that site.

## Trial status

The first patient was enrolled in March 2012, and recruitment is ongoing.

## Abbreviations

2-D: Two-dimensional; ACE: Angiotensin-converting-enzyme; AE: Adverse event; AIMS: Aortic Irbesartan Marfan Study; ANCOVA: Analysis of covariance; AR: Adverse reaction; ARB: Angiotensin receptor blocker (also known as angiotensin II receptor antagonist); AT1: Angiotensin II receptor type 1; AT2: Angiotensin II receptor type 2; BMS: Bristol-Myers Squibb; BSA: Body surface area; CT: Computed tomography; CTA: Clinical trial authorisation; CTEU: Clinical Trials and Evaluation Unit; DMC: Data Monitoring Committee; DSMC: Data and Safety Monitoring Committee; ECG: Electrocardiography; eCRF: Electronic case record form; EDTA: Ethylenediaminetetraacetic acid; EudraCT: European Union Drug Regulating Authorities Clinical Trials; IMP: Investigational medicinal product; IVRS: Interactive voice recognition system; MFS: Marfan syndrome; MHRA: Medicines and Healthcare Products Regulatory Agency; MMP: Matrix metalloproteinase; MRC: Medical Research Council; MRI: Magnetic resonance imaging; NHS: National Health Service; NIH: National Institute of Health; NIHR: National Institute for Health Research; NRES: National Research Ethics Service; OD: Once daily; RCT: Randomized clinical trial; REC: Research Ethics Committee; SAE: Serious adverse event; SAR: Serious adverse reaction; SDV: Source data verification; SmPC: Summary of product characteristics; SUSAR: Suspected unexpected serious adverse reaction; TGF-β: Transforming growth factor beta; TEE: Transesophageal echocardiography; TSC: Trial Steering Committee; TTE: Transthoracic echocardiogram; UAR: Unexpected adverse reaction.
